### 2.2. Study Setting

Data collection will take place at the rehabilitation department of four tertiary hospitals located in different regions of China: (1) The First Affiliated Hospital of Sun Yat-Sen University; (2) The Seventh Affiliated Hospital of Sun Yat-sen University; (3) The Fifth People's Hospital of Foshan Institute of Science and Technology; and (4) the Beijing Rehabilitation Hospital of Capital Medical University. Participants will be recruited from the inpatient wards of the participating centers. The data collection process is expected to last for 4 years. All interventions will be delivered by trained healthcare professionals within these centers. Figure 1 shows the study procedure. 

### 2.3. Recruitment

Suitable participants will be identified from patients who are admitted to the rehabilitation department due to stroke. The initial screen for eligibility will be conducted as part of the routine clinical assessment by members of the medical team. Written information about the study will first be provided to all potentially suitable participants before being approached by the research team to inquire as to whether they are interested in participating in the study. Written consent will be obtained from participants who express willingness to participate. All of the non-recruited patients and the reasons for exclusion will be recorded in a screening log. 

### 2.4. Sample Population 

The inclusion criteria for the stroke group are as follows: (1) the first occurrence of stroke with hemiparesis within the first month as confirmed by computed tomography or magnetic resonance imaging (MRI); (2) participants must be aged between 40- to 79-years-old; (3) Brunnstrom stage 3; (4) modified Ashworth scale score ≤2; (5) medically stable and able to sit unsupported for at least 30 min; (6) able to walk 10 m with or without walking aid; (7) no severe cognitive impairment, as defined by the Mini-mental State Examination (scale score greater than 10) [38], and (8) at least five degrees of active wrist extension and ankle dorsiflexion are available. The exclusion criteria are as follows: (1) comorbidity conditions including congestive heart failure, deep vein thrombosis, and malignant progressive hypertension; (2) lower limb fracture; (3) history of mental illness or on anti-psychotic drugs. The rationale to include only participants who could sit unsupported for 30 min was due to that fact that interlimb-coordinated interventions are conducted in a seated position. The Brunnstrom stage of recovery is included as a criterion to ensure that the participants have recovered some of the motor function before participation in the intervention program. The modified Ashworth scale is to ensure that motor function is not affected by high level of muscle spasticity.

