### 2.5. Randomization

Eligible participants will be randomly assigned to either the experimental or the control group at a ratio of 1:1 without stratification. A statistical expert from the Faculty of Medical Statistics and Epidemiology, Sun Yat-sen University, computed the random allocation sequence. The sequence will be uploaded onto a central operating system. Research team members will access the system at the time of participant enrolment by dialing the central phone number to obtain the allocation. The operating system will provide the numbers of 001 and 002, which correspond to the intervention group and control group, respectively. Each participant will be assigned a unique identification number to maintain confidentiality. 

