### 4.2. Data Analysis

All statistical analyses will be performed in IBM SPSS version 21 software (SPSS Inc., Chicago, IL, USA). Descriptive statistics will be conducted to describe the sample population. The demographic characteristics and baseline results for the primary and secondary outcome measures will be analyzed using analysis of variance (ANOVA) or Chi-square test for categorical data. A mixed-effect model analysis will be adopted to compare changes in all of the outcome measures between groups at the completion of the intervention and at the 3- and 6-month follow-ups. The mixed-effect model analysis will include treatment, time, and centre as fixed effects, and the participants will be included as the random effect. Changes in the outcome measures will be adjusted for age, sex, centre, and time. The level of statistical significance will be set at *p* < 0.05. Cohen’s d will be calculated to measure the effect size of the difference for every comparison. The effect size will be interpreted as follows: 0.2—small effect size; 0.5—medium effect size; and 0.8—large effect size. Stratification analysis will be conducted to explore the potential effect difference between centres. There are no planned interim analyses or stopping rules, as the power calculation has accounted for loss to follow-up. In the event of missing data during the follow-up period, the modified intention to treat principle will be followed with the last observation carried forward method. 

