## 5. Discussion

Several clinical guidelines propose that active rehabilitation is to be provided within 24–48 h of stroke occurrence [57], as the most considerable amount of the recovery was reported to take place in the first month following stroke [58]. Available evidence supports the benefits of early rehabilitation intervention on motor recovery, but convincing evidence for an early interlimb coordinated intervention is lacking. Thus, this study will provide evidence on the feasibility and efficacy of interlimb coordinated movement as part of an early intervention program for gait and motor function improvement. The medium long-term efficacy of the interlimb coordinated intervention will also be assessed in this study. Several Cochrane reviews regarding the efficacy of other interventions on motor function recovery seldom report data beyond the initial discharge period [59] or has followed up beyond the three [60] or six month periods [61]. As motor function capacities evolve the most during the first month of stroke onset [62], it is anticipated that intervention provided during the acute stage of stroke has better clinical outcomes when compared to interventions that are provided at later stroke stages. Therefore, 3- and 6-month post-intervention follow-up data will increase the understanding of whether interlimb coordinated intervention is superior to conventional therapy in the longer term. 

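### Days since stroke is missing from the stated adjustment set although entry spans the first month; the test stays valid, but some precision is lost, by an amount the documents do not fix

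*Protocol article*

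**What the plan says.** Four statements in the protocol article bear on this point.

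- **Entry (section 2.4).** Inclusion criterion 1 accepts "the first occurrence of stroke with hemiparesis within the first month as confirmed by computed tomography or magnetic resonance imaging". No narrower window is set.
- **Recovery (section 5, Discussion).** The article says that "the most considerable amount of the recovery was reported to take place in the first month following stroke", and again: "As motor function capacities evolve the most during the first month of stroke onset".
- **Allocation (section 2.5).** Assignment is "at a ratio of 1:1 without stratification", so the design does not balance entry day.
- **Analysis (section 4.2).** "The mixed-effect model analysis will include treatment, time, and centre as fixed effects", with participant as the random effect. Then: "Changes in the outcome measures will be adjusted for age, sex, centre, and time". The model compares the arms at the end of the intervention and at 3 and 6 months, so time here is the repeated-visit factor. It does not carry time since stroke.

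**The concern.** The protocol names a driver of motor change, lets it vary over a whole month, and then states an adjustment list that leaves it out. A patient randomised on day 3 has the 2-week change measured over days 3 to 17; a patient randomised on day 30 has it measured over days 30 to 44. If recovery slows over the month, the expected change without any effect of the new training differs between these two patients.

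Analysing change from baseline does not remove this, because the amount of change is what depends on entry day. The visit factor does not remove it either, since both patients are at the same visit.

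At stake are the precision of the gait-speed comparison and protection against a covariate being chosen after the data have been seen. The validity of the test is not at stake.

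**Working it through.** **1. The plan's own figure.** Section 2.12 gives means of 0.69 and 0.39 and SD 0.75, so f = (0.3/0.75)/2 = 0.20. For a repeated-measures ANOVA, between factors, the noncentrality is λ = f²·N·m/(1+(m−1)ρ), with 1 and N−2 degrees of freedom. With m = 4 visits, alpha 0.05 and ρ = 0.5 (not stated; assumed), N = 206 gives power 0.951. The stated 206 is reproduced, and 206 × 1.1 = 226.6 matches the 226 to be recruited. At ρ = 0.5 the SD of a change score is 0.75·√(2(1−0.5)) = 0.75, so the protocol's SD serves for change as well.

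**2. Validity without the covariate.** In simulations with 103 per arm, SD 0.75 and entry uniform over 0 to 30 days (5,000 runs per setting), the unadjusted type I error was 0.052 when the correlation r of entry day with outcome was 0.3, and 0.049 when it was 0.5.

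**3. Chance imbalance.** Uniform entry over 30 days has SD 30/√12 = 8.7 days. The difference in mean entry day between arms of 103 has SE 8.66·√(2/103) = 1.2 days, so a 95% range of ±2.4 days.

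**4. Variance explained under a recovery curve (assumed).** Let the gain without the new training from day d to d+14 be g(d) = A[exp(−d/τ) − exp(−(d+14)/τ)], with entry uniform over days 3 to 30. A is the total recoverable speed and τ the time constant. The share of variance explained is R² = SD(g)²/(SD(g)² + residual SD²).

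| τ (days) | g(3)/g(30) = exp(27/τ) | SD of g |
|---|---|---|
| 14 | 6.9 | 0.122A |
| 21 | 3.6 | 0.087A |
| 28 | 2.6 | 0.063A |

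With A from 0.4 to 0.6 m/s (assumed):

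| Residual SD (m/s) | Lowest R² (A = 0.4, τ = 28) | Highest R² (A = 0.6, τ = 14) |
|---|---|---|
| 0.15 (assumed) | 2.7% | 19.3% |
| 0.25 (assumed) | 1.0% | 7.9% |
| 0.75 (section 2.12) | 0.1% | 1.0% |

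The middle case (A = 0.6, τ = 21, residual SD 0.20) gives 6.4%. The confidence interval narrows by the factor √(1−R²): by 10% at R² = 19.3%, by 3% at 6.4%, by 0.5% at 1%.

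Under this curve, the 95% range of the shift in the 2-week difference from chance imbalance is 1.96·SD(g)·√(2/103). That is ±0.007 m/s (A = 0.4, τ = 28) to ±0.020 m/s (A = 0.6, τ = 14), against the planned 0.3 m/s.

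**5. The same question through a correlation.** With SD 0.75 and 103 per arm at a single visit, power is 81.9% unadjusted. Adjustment gives 82.3%, 85.3% and 91.2% for r = 0.1, 0.3 and 0.5. The larger values are hard to reconcile with SD 0.75: r = 0.5 means a slope of 0.5 × 0.75/8.66 = 0.043 m/s per day, or 1.3 m/s over 30 days, while the Introduction gives a mean speed of only 0.65 m/s in chronic stroke. At SD 0.75 only the low end of r is credible.

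**6. Later visits.** For change to a visit T days after baseline, the curve gives A·exp(−d/τ)·(1−exp(−T/τ)). At τ = 21 the SD across entry days is 0.087A at 2 weeks and about 0.177A at 3 months. The effect on change from baseline therefore differs between visits, and under this curve it grows.

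**The case against.** The strongest reply is that section 4.2 is valid as written. Allocation is random, the standard error already allows for chance imbalance in any unadjusted factor, and the choice of one more prognostic covariate is partly a matter of preference. This stands, and it limits the point to precision. A reader might infer that the treatment estimate is biased or the test invalid; the documents and the simulation do not support that.

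The size is also open to challenge. The documents give no recovery curve and no distribution of entry days. Residual SDs of 0.15 to 0.25 m/s are assumed, well below the protocol's 0.75. The Introduction's mean speeds of 0.33 m/s (subacute) and 0.65 m/s (chronic) differ by 0.32. Used as A with τ = 21 and residual SD 0.20, that gives R² = 1.9%. Patients must be medically stable, sit unsupported for 30 minutes and walk 10 m, so very early entry may be rare. If entry began on day 10 or day 14 (assumed), the middle case falls from 6.4% to 2.5% or 1.3%. These objections stand. A reader might turn the 19.3% into 226/(1−0.193) = 280, a gain worth 54 patients. That figure needs the most favourable value of every assumption and should not be used.

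Two further inferences fail. One is that the entry-day effect fades by 3 and 6 months; for change from baseline, step 6 shows the opposite under the same curve. The other is that a treatment-by-days interaction would test the Discussion's expectation, "it is anticipated that intervention provided during the acute stage of stroke has better clinical outcomes when compared to interventions". That sentence goes on to compare with later stages of stroke, not with a later day in the first month, and section 1 lists no hypothesis on timing within the month. The Discussion also speaks of recovery without separating the spontaneous part, so that separation belongs to the assumed curve and not to the protocol.

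The reply that a fuller document may add the covariate does not dispose of the point, because the article states a specific adjustment list and that list omits it.

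**Conclusion.** The point holds as a matter of precision and prespecification. Entry is open throughout the month in which the protocol itself says motor function changes most, allocation does not balance entry day, and the stated adjustment set omits it. Type I error is unaffected.

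The direction of the gain from adjusting is clear; its size is uncertain and may be small. Entry day explains roughly 0.1% to 1% of the variance in 2-week change at the protocol's SD of 0.75, and roughly 1% to 19% at assumed residual SDs of 0.15 to 0.25 m/s. Both ranges rest on exponential recovery with τ of 14 to 28 days, 0.4 to 0.6 m/s recoverable speed, and entry spread evenly over days 3 to 30. None of these three inputs is in the documents. The case for changing the plan rests on the very low cost more than on a large expected gain.

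**What to change.** In section 4.2, add days from stroke onset to randomisation to the adjustment set as a prespecified continuous baseline covariate for gait speed and the motor outcomes. Include its interaction with visit so that its effect may differ across visits. A linear term is adequate under the assumed curves, where it captures 94% to 98% of the variation in g(d). In the same sentence, say that time in the present list means the study visit.

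The onset date is already needed to apply inclusion criterion 1, so no new data are collected. The cost is a few degrees of freedom among 226 patients. Sample size, eligibility, allocation and treatment stay as they are. The change should be made before any outcome data by arm are seen, since a covariate added later could look selected.

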### 2.5. Randomization

Eligible participants will be randomly assigned to either the experimental or the control group at a ratio of 1:1 without stratification. A statistical expert from the Faculty of Medical Statistics and Epidemiology, Sun Yat-sen University, computed the random allocation sequence. The sequence will be uploaded onto a central operating system. Research team members will access the system at the time of participant enrolment by dialing the central phone number to obtain the allocation. The operating system will provide the numbers of 001 and 002, which correspond to the intervention group and control group, respectively. Each participant will be assigned a unique identification number to maintain confidentiality. 

### 2.6. Ethics

Ethical approval was obtained from the Medical Ethical Committee of the First Affiliated Hospital of Sun Yat-Sen University (Ethics Number: [2020]430). The clinical trial is registered with the Chinese Clinical Trial Registry (Registration Number: ChiCTR2000040137, prospective registration on the 22 November 2020). All relevant parties will be informed of any important modifications to protocol modifications. All of the participants who are invited to participant in the study will be given time to consider if they wish to take part in the trial and will be encouraged to ask any questions. All of the participants will be free to withdraw from the trial at any time without providing a reason. The participants will be able to withdraw themselves completely, in which case, all of the collected data will be excluded from the study, or to withdraw only from further assessment or intervention, in which case, all of the collected data will be included in the final analysis depending on personal preference. Medical expenses that are incurred as part of the research are covered by the research grant. Travel reimbursement will also be provided to all participants during the follow-up periods to promote a strong adherence rate. 

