## 2. Materials and Methods 

### 2.1. Study Design

This study is a parallel, single-blinded, multi-center randomized controlled trial to evaluate the effect of interlimb-coordinated intervention on gait and motor function recovery in patients with acute stroke. 

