## 4. Safety and Adverse Event Reporting

Patients with acute stroke have a likelihood of morbidity and mortality. Procedures are in place to minimize the occurrence of adverse events. Medical doctors will assess participants to ensure safe rehabilitation participation. Medically unstable patients will not be recruited for the study. Participants will be asked to exercise according to their physical capability. Trained physiotherapists/occupational therapists who work closely with the inpatient clinical team will be onsite during the exercise sessions. Any issues raised during the exercise session will be reported to the inpatient medical team. The following safety reporting procedures are in place:Serious adverse events (SAEs) are defined as an event that incurs harm to the participants, which may or may not require medical or surgical intervention as a preventative measure to avoid the following outcomes: death, further impairment of body function, damage to a body structure, and prolonged the hospitalization period.All SAEs related to the interventions will be recorded on a SAEs event report form in accordance with the procedures of each research centre.All of the SAEs related to the interventions must be reported to the Principal Investigator within 24 h of learning of the event.SAEs that are related to the interventions will be reported to the University Clinical Trial Unit and Research Ethics Committee within 15 days of the occurrence of the SAEs. The following information will be reported to relevant parties: (1) the concerned research protocol; (2) a report on the description of the SAE and subsequent outcome; (3) a proposal of changes in response to the SAE to prevent further occurrence of SAEs

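### Complete withdrawal removes all data already collected, with no exception for finished visits or safety data, so a choice made after randomisation can bias completed gait-speed comparisons.

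*Protocol article*

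**What the plan says.** Section 2.6 (Ethics) sets the withdrawal rule: "All of the participants will be free to withdraw from the trial at any time without providing a reason". Two routes follow. A participant may "withdraw themselves completely, in which case, all of the collected data will be excluded from the study", or may stop only further assessment or intervention, in which case "all of the collected data will be included in the final analysis depending on personal preference". The complete route carries no exception for outcomes already measured or for safety data.

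Section 4.2 (Data Analysis) plans a mixed-effect model for all outcomes. For missing follow-up data it adds that "the modified intention to treat principle will be followed with the last observation carried forward method".

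On blinding, section 2.1 says "This study is a parallel, single-blinded, multi-center randomized controlled trial", and section 2.11 names the assessment teams as blinded to allocation. No statement says that participants are blinded, and only the intervention arm trains on the ergometer (section 3.2, Table 3).

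On harms, section 4 says "All SAEs related to the interventions will be recorded on a SAEs event report form". These events go to the Principal Investigator within 24 h, and "SAEs that are related to the interventions will be reported to the University Clinical Trial Unit and Research Ethics Committee within 15 days". Section 4 does not say what happens to safety data after complete withdrawal.

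**The concern.** Ordinary dropout costs the later visits and leaves the earlier ones in place. This rule works backwards. A participant who has completed the baseline, post-intervention and 3-month tests and then withdraws completely before month 6 takes three valid gait speeds out of the analysis. Membership of the analysed group is settled after randomisation, by someone who may well know the arm and can sense how recovery is going.

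If those who choose the complete route have done worse than their arm and come more from one arm, that arm's mean rises and the between-group difference shifts. The shift appears even at the 2-week visit, where every value had been measured. LOCF and the mixed model are of no help, since no value is left to carry forward or to model.

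The same mechanism can thin out adverse events in the trial dataset, above all non-serious events and events judged unrelated, for which section 4 describes no separate report.

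**Working it through.** **1. The plan's own sample size, and why its allowance does not help.** Section 2.12 gives means of 0.69 and 0.39 m/s and SD 0.75, so f = 0.3/(2 × 0.75) = 0.2. For a repeated-measures ANOVA, between factors, λ = f²·N·m/(1 + (m − 1)ρ), with 1 and N − 2 degrees of freedom and alpha 0.05. With m = 4 visits and ρ = 0.5 (assumed, as no correlation is given), the required N is 206 and power is 0.951, which reproduces the plan.

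With the inflated total of 226, power is 0.966. If 10% are lost, about 203 remain (226 × 0.9) and power is 0.948. Loss of numbers therefore matters little. The allowance protects power and does nothing against selective removal.

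**2. Assumptions of the illustration.** None of these comes from the protocol except 113 per arm and the SD of 0.75.
- No true effect; 113 per arm; visit correlation 0.7 between any two of baseline, 2 weeks and 6 months.
- Gait-speed SD 0.2–0.4 m/s, with 0.75 (section 2.12) as a further case.
- Complete withdrawal after the 2-week test, in the intervention arm only, drawn at random from the 30% with the poorest 2-week change.
- Two rates: 2 of 113 (about 2%) and 11 of 113 (about 10%).

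**3. How far below their arm the withdrawers lie.** The SD of the 2-week change is SD × √(2 × (1 − 0.7)) = 0.775 SD. The mean of the lowest 30% of a normal distribution lies 0.3477/0.30 = 1.159 of its SDs below the mean. The shortfall at 2 weeks is 1.159 × 0.775 SD = 0.898 SD. The regression of 6-month change on 2-week change has slope 0.3/0.6 = 0.5, so the expected 6-month shortfall is 0.449 SD.

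**4. Bias when their data are excluded.** Removing a fraction q raises the arm mean by q/(1 − q) × shortfall.
- 2 weeks, 2 of 113: (2/111) × 0.898 SD = 0.0162 SD.
- 2 weeks, 11 of 113: (11/102) × 0.898 SD = 0.0968 SD.
- 6 months, 11 of 113: (11/102) × 0.449 SD = 0.0484 SD.

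Simulation, which respects the finite size of the arm, gives nearly the same values:

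| Bias (m/s) | SD 0.2 | SD 0.4 | SD 0.75 |
|---|---|---|---|
| 2 weeks, about 2% excluded | 0.003 | 0.006 | 0.012 |
| 2 weeks, about 10% excluded | 0.019 | 0.038 | about 0.072 |
| 6 months, about 10% excluded | 0.010 | 0.019 | 0.036 |

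Section 2.12 cites 0.16 m/s as the clinically important difference. On that scale the 2-week bias for SD 0.2–0.4 is 2–4% at 2% withdrawal (0.003/0.16 and 0.006/0.16) and 12–24% at 10% (0.019/0.16 and 0.038/0.16). With SD 0.75 at 10% it is 45% (0.072/0.16).

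**5. Bias when the data are kept.** At 2 weeks it is zero, because everyone was measured. At 6 months it depends on the method. LOCF gives the withdrawers their 2-week change (0.898 SD below) in place of the expected 6-month change (0.449 SD below). The arm mean moves by −(11/113) × 0.449 SD = −0.0437 SD, that is −0.009 to −0.017 m/s for SD 0.2–0.4. This nearly mirrors the exclusion bias of +0.010 to +0.019. A likelihood-based analysis of the observed visits is about unbiased here, because in this scenario withdrawal depends only on values that are kept.

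**The case against.** The strongest reply is that the rule respects participants' rights and is only one of two routes, the other of which keeps the data. That is right, and the right to stop is not in question. The point concerns data already collected, and the absence of any safeguard or count for the complete route.

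A second reply is that the illustration stacks adverse conditions. The 10% in section 2.12 is a missing rate for all causes and both arms, and nothing in the article suggests that complete withdrawals will be that frequent or one-sided. This stands: at 2% the bias is small.

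Four stronger readings are tempting and not supported.
- **That data are destroyed.** The text says excluded from the study, and only for those who choose that route.
- **That harms vanish from every record.** Section 2.6 does not recall intervention-related serious events already reported under section 4, so these remain in those reports. The possible loss is from the trial dataset and its analysis.
- **That section 2.6 flatly contradicts section 4.2.** The principle there is a modified one and does not promise that every randomised participant is analysed. Its definition may stand in an analysis plan that is not shown.
- **That keeping the data alone removes the bias.** It does so at 2 weeks. At 6 months under LOCF it does not (step 5).

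**Conclusion.** The concern holds in this limited form. As written, section 2.6 allows a choice made after randomisation, by participants not stated to be blinded, to alter comparisons at visits already completed and to take adverse events out of the trial dataset. The problem is bias; power hardly changes.

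Its size cannot be known from the article. Under the assumptions in step 2 it runs from negligible at 2% one-arm withdrawal to a noticeable share of the cited 0.16 m/s at 10%, and it grows in proportion to the SD. If complete withdrawal were unrelated to response, or alike in both arms, the expected bias under no true effect would be nil. It is a correctable weakness in a stated rule, best dealt with early because each consent under the present wording fixes the option for that participant.

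**What to change.** - **Section 2.6 and the matching consent wording, for future participants:** let withdrawal stop further procedures, while outcome and safety data collected up to that point are kept and analysed in the allocated arm. Exclude data only on a separate explicit request, as far as ethics rules require. This leaves a narrow route to the same bias, so report the number and timing of such requests by arm.
- **Section 4.2:** analyse all randomised participants with available data in their allocated group, through the planned mixed model on all observed visits, and drop LOCF. The two changes belong together, because retention under LOCF only reverses the sign of the 6-month bias.

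**Cost:** a protocol and consent amendment needing ethics approval, with no extra visits or patients. Participants already consented keep the option they were given, so some exclusions may still occur and should be counted in the same way.
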